# Treatment shortening of drug-sensitive pulmonary tuberculosis using high-dose rifampicin for 3 months after culture conversion (Hi-DoRi-3): a study protocol for an open-label randomized clinical trial

**DOI:** 10.1186/s13063-022-06631-z

**Published:** 2022-08-17

**Keywords:** Tuberculosis, Shorter regimen, Rifampicin

## Abstract

**Background:**

The standard treatment regimen for drug-sensitive tuberculosis (TB), comprising four companion drugs, requires a minimum duration of 6 months, and this lengthy treatment leads to poor adherence and increased toxicity. To improve rates of adherence, reduce adverse events, and lower costs, a simplified and shortened treatment regimen is warranted.

**Methods:**

This study is a multicenter, open-label randomized clinical trial of non-inferiority design that compares a new regimen with the conventional regimen for drug-sensitive pulmonary TB. The investigational group will use a regimen of high-dose rifampicin (30 mg/kg/day) with isoniazid and pyrazinamide, and the treatment will be maintained for 12 weeks after the achievement of negative conversion of sputum culture. The control group will be treated for 6 months with a World Health Organization-endorsed regimen consisting of isoniazid, rifampicin (10 mg/kg/day), ethambutol, and pyrazinamide. The primary endpoint is the proportion of unfavorable outcomes at 18 months after randomization. Secondary outcomes include time to unfavorable treatment outcome, time to culture conversion on liquid medium, treatment success rate at the end of treatment, proportion of recurrence at 18 months after randomization, time to recurrence after treatment completion, and adverse events of grade 3 or higher during the treatment. We predict a 10% unfavorable outcome for the control group, and 0% difference from the investigational group. Based on 80% verification power and a 2.5% one-sided significance level for a non-inferiority margin of 6%, 393 participants per group are required. Considering the 15% dropout rate, a total of 926 participants (463 in each group) will be recruited.

**Discussion:**

This study will inform on the feasibility of the treatment regimen using high-dose rifampicin with a shortened and individualized treatment duration for pulmonary TB.

**Trial registration:**

ClinicalTrials.gov NCT04485156. Registered on July 24, 2020.

**Supplementary Information:**

The online version contains supplementary material available at 10.1186/s13063-022-06631-z.

## Background

Tuberculosis (TB) remains one of the most important infectious diseases. Globally, around 5.8 million people fell ill with TB and 1.5 million people died from TB in 2021. Moreover, ~ 25% of the world’s population has latent TB infection [1]. In South Korea, 22,904 TB cases were reported with a notification rate of 44.6 per 100,000 population in 2021 [2]. Although TB remains a global health concern, TB can be cured with medical treatment, and the success rate for drug-sensitive TB can reach 85% [1].

The standard treatment regimen for drug-sensitive TB, which was introduced in the 1980s, consists of four drugs: isoniazid, rifampicin, pyrazinamide, and ethambutol [3]. While this regimen has proven to be effective, it typically requires a minimum 6-month treatment duration, irrespective of disease severity or extent [4]. This lengthy treatment leads to poor adherence and increased toxicity [5]. To improve rates of adherence, reduce adverse events, and lower costs, several clinical trials have investigated approaches that aim to shorten the treatment duration in TB patients; however, these studies have failed to prove non-inferiority to the standard 6-month regimen, with the exception of a 4-month regimen based on rifapentine and moxifloxacin [6–9].

To shorten the treatment duration, the sterilizing activity of anti-TB drugs should be taken into consideration, and rifampicin is a cornerstone drug for the maintenance of sterilizing activity. Rifampicin, a derivate of rifamycin, is effective against *Mycobacterium tuberculosis* populations in a dormant state, as well as those undergoing rapid metabolism [3, 10]. Therefore, rifampicin has the potential to shorten treatment duration to less than 6 months [10]. The area under the concentration–time curve and peak concentration of rifampicin showed a more than proportional increase with a dose change from 10 to 35 mg/kg/day [11, 12]. The higher exposure to rifampicin with the dose increment led to a more rapid fall in bacterial loads [11, 12]. Despite these favorable dose–response relationships of rifampicin, the maximal recommended dose is limited to 10 mg/kg/day or 600 mg/day, owing to the concern of adverse events [13]. However, the use of rifampicin at doses higher than the recommended dose did not cause additional serious adverse events [14, 15]. The number of serious adverse events, including hepatotoxicity, was independent of rifampicin dose in two recent randomized controlled trials [14, 15]. According to real clinical practice data from a Dutch cohort, 6–12 months of high-dose rifampicin therapy was safe and well-tolerated in 99% of patients [16].

Based on the literature, we propose a simplified and shortened treatment strategy using high-dose rifampicin. The effectiveness, safety, and tolerability of a three-drug therapy using high-dose rifampicin with isoniazid and pyrazinamide will be investigated in comparison with the standard 6-month treatment for TB. The protocol of a phase 3, multicenter, randomized, open-label non-inferiority clinical trial, entitled “Treatment shortening of drug-sensitive pulmonary TB using high-dose rifampicin for 3 months after culture conversion (Hi-DoRi-3)” is presented here.

## Methods/design

### Study design

This investigator-initiated study is a prospective, multicenter, randomized, open-label, two-arm non-inferiority clinical trial. Participants with drug-sensitive pulmonary TB will be randomly assigned to one of two groups at a 1:1 ratio, and the study will be terminated 18 months after randomization.

### Control group

Participants randomized to the control group will receive standard treatment in accordance with the Korean guidelines for TB [17] and the World Health Organization guidelines [4]. Consequently, patients in the control group will be administered isoniazid, rifampicin, pyrazinamide, and ethambutol for 2 months, followed by isoniazid, rifampicin, (and ethambutol) for 4 months, comprising a total treatment period of 6 months (Table 1). Although temporary use of secondary anti-TB drugs is permitted in the case of adverse events such as liver toxicity, the total duration of use should be less than 4 weeks. If rifampicin is discontinued because of adverse events, the period of discontinuation must also be less than 4 weeks.

**Table 1 Tab1:** Dose and schedule of anti-tuberculous drugs for the control group

Drug name	Capacity			Administration method
	Per bodyweight	Recommended dose	Maximum dose	
Isoniazid	5 mg/kg	300 mg/day	300 mg/day	once a day before meal
Rifampicin	10 mg/kg	450 mg (< 50 kg) 600 mg (≥ 50 kg)	600 mg/day	once a day before meal
Pyrazinamide	20–30 mg/kg	1000 mg (< 50 kg) 1500 mg (50–70 kg) 2000 mg (> 70 kg)		once a day after meal
Ethambutol	15–20 mg/kg	800 mg (< 60 kg) 1200 mg (60–80 kg) 1600 mg (> 80 kg)		once a day after meal

### Investigational group

Participants randomized to the investigational group will be treated with high-dose rifampicin (body weight, dose: < 44 kg, 1200 mg/day; 45–54 kg, 1500 mg/day; 55–64 kg, 1800 mg/day; 65–74 kg, 2100 mg/day; > 75 kg, 2400 mg/day), isoniazid (300 mg/day), and pyrazinamide (body weight, dose: < 50 kg, 1000 mg/day; 50–70 kg, 1500 mg/day; > 70 kg, 2000 mg/day) until culture conversion (liquid medium) is confirmed (Table 2). High-dose rifampicin and isoniazid will be administered until 12 weeks after the date of sputum culture negative conversion. The dosage of rifampicin will be maintained throughout the study duration. Ethambutol will not be included in the initial regimen to reduce the number of pills. However, in the instance that isoniazid or pyrazinamide is discontinued prior to the end of treatment, ethambutol may be added to the treatment regimen if the investigator decides that reinforcement of the drug is necessary. Although temporary use of secondary anti-TB drugs is permitted in the case of adverse events such as liver toxicity, the total duration of use should be less than 4 weeks. If rifampicin is discontinued because of adverse events, the period of discontinuation must also be less than 4 weeks. The study overview is provided in Fig. 1.

**Table 2 Tab2:** Dose and schedule of anti-tuberculous drugs for the investigational group

Drug name	Dose (body weight)	Administration method
Isoniazid	300 mg/day	once a day before meal
Rifampicin	1200 mg/day (< 44 kg) 1500 mg/day (45–54 kg) 1800 mg/day (55–64 kg) 2100 mg/day (65–74 kg) 2400 mg/day (> 75 kg)	once a day before meal
Pyrazinamide	1000 mg/day (< 50 kg) 1500 mg/day (50–70 kg) 2000 mg/day (> 70 kg)	once a day after meal

**Fig. 1 Fig1:**
[figure not shown]
Study overview

### Study population

A total of 926 participants with drug-sensitive pulmonary TB will be enrolled in the study (463 participants per group). Adult participants aged between 19–85 years whose sputum (or bronchoscopic specimen) is positive for Xpert MTB/RIF assay or *M. tuberculosis* culture, and who have been taking any TB medication for no more than 7 days at the time of enrollment, will be included. The exclusion criteria are as follows: (1) rifampicin resistance confirmed by Xpert MTB/RIF assay; (2) drug resistance to isoniazid, rifampicin, or pyrazinamide, confirmed by a drug-susceptibility test; (3) human immunodeficiency virus infection; (4) malignancy needing anti-cancer chemotherapy; (5) chronic hepatitis or liver cirrhosis; (6) any contraindications for the study drugs (hypersensitivity to the study drugs, biliary obstruction, galactose intolerance, Lapp lactase deficiency, or glucose-galactose malabsorption); (7) current use of drugs, such as indinavir, saquinavir, nelfinavir, amprenavir, praziquantel, or atovaquone, or any other drugs contraindicated in combination with study drugs, within 1 day before study enrollment, or expected to be used within the following 28 days; and (8) pregnancy, breastfeeding, or pregnancy planned within the following 6 months.

### Assignment of interventions: allocation

#### Sequence generation

The randomization table will be generated and will be reproducible via SAS 9.4 software, using the stratified block randomization method with a stratification factor of (1) acid-fast bacilli (AFB) smear positivity and (2) presence of diabetes. The Medical Research Collaborating Center (MRCC) of the Seoul National University Hospital will operate a web-based randomization system remotely.

#### Allocation concealment mechanism

It is an open-label trial. Both participants and treating physicians will be aware of allocation information.

#### Implementation

Participants will be provided with a detailed explanation of the purpose, method, and procedure for this study, and written consent for participation in the clinical trial will be obtained. Prior to randomization, participant demographic information, medical history, and physical examination results will be collected, including results of the Xpert MTB/RIF assay, AFB smear (including *M. tuberculosis* culture), chest X-ray, blood test, and urine (or serum) human chorionic gonadotropin (hCG; for women of childbearing age) test. After completing the consent procedure, participants who meet the inclusion criteria will be randomly assigned to the investigational or control group at a ratio of 1:1 in week 0.

### Treatment visits

Following enrollment, participants of each group will visit the hospital every 2 weeks until 8 weeks after enrollment. Subsequently, visits will be made every 4 weeks until the end of treatment. The tests performed at each visit will include the following: physical examination, AFB smear and culture using a liquid medium, and blood test. For women of childbearing age, a urine or blood hCG analysis will be performed. Simple chest X-ray will be performed every 4 weeks. Participants who cannot produce sputum will be encouraged to expectorate sputum. If the participants cannot produce sputum, it will not be deemed as protocol violation.

### Follow-up

After the end of treatment, visits will be made every 3 months up until 18 months after the enrollment date. The physical examination, AFB smear and culture, and chest X-ray tests will be performed at each visit. The study timeline is shown in Tables 3 and 4.

**Table 3 Tab3:** Time line for control group

Type	Screening^a^	Baseline^a^	Treatment				End of treatment (EOT)^h^	Follow-up				End of study (EOS)
Visit name	Screening	D0	W2	W4	W6	W8	W12 ~ (every 4 W)	EOT + 3 M	EOT + 6 M	EOT + 9 M	EOT + 12M^i^	M18^i^
Weeks (w)	− 14 ~ 0 days	0	2 W	4 W	6 W	8 W	12 W/16 W/20 W/24 W /28 W/32 W	EOT + 13 W	EOT + 26 W	EOT + 39 W	EOT + 52 W	78 W
Visit window	n-a	n-a	± 4 days	± 4 days	± 4 days	± 4 days	± 2 weeks	± 6 weeks	± 6 weeks	± 6 weeks	± 6 weeks	± 6 weeks
Consent	O											
Randomization		O										
Medical history	O											
Physical exam	O	O	O	O	O	O	O	O	O	O	O	O
Xpert MTB/RIF assay	O^e^											
Sputum AFB smear	O^e^	O^e^	O	O	O	O	O	O	O	O	O	O
TB culture (liquid)	O^e^	O^e^	O	O	O	O	O	O	O	O	O	O
DST^b^	With first/reverted cultured MTB											
Chest X-ray	O^e^	O^e^		O		O	O	O	O	O	O	O
Chemistry^c^	O^e^	O^e^	O	O	O	O	O^h^					
Complete blood count	O^e^	O^e^	O	O	O	O	O^h^					
HIV	O^e^											
Urine (or blood) HCG^d^	O	O	O	O	O	O	O^h^					
HBV/HCV^f^		O^e^										
Compliance of drug intake			O	O	O	O	O^h^					
Adverse drug reaction			O	O	O	O	O^h^	O				
Other medication^g^	O		O	O	O	O	O^h^					

^a^ It can be performed with the baseline visit if all screening results can be checked on the day

^b^ Drug susceptibility test for isoniazid, rifampicin, ethambutol, pyrazinamide, streptomycin, kanamycin, amikacin, capreomycin, ofloxacin, levofloxacin, moxifloxacin, prothionamide, cycloserine, rifabutin, and para-aminosalicylic acid (Omitted for the patients whose results are already reported)

^c^ Test items according to the standard treatment guidelines (refer to 6. Study procedures)

^d^ Performed for women of childbearing age tested within 7 days

^e^ The existing test results can be extracted and collected without additional testing if the previous test was performed within 4 weeks (based on the report day for the TB culture)

^f^ Since HBsAg and Anti-HCVAb are not excluded even if they are positive, drugs can be administered even before the results are reported

^g^ Confirmation of concomitant drugs, especially immunosuppressants including oral steroids

^h^ The EOT date is determined according to standard of care guidelines. A visit every 4 weeks until EOT and every 3 months after EOT. The test is not performed after EOT

^i^ If the 78-week visit (EOS) after randomization arrives earlier than the EOT + 9 M visit, the EOT + 9 M visit is omitted, and the EOS visit proceeds

**Table 4 Tab4:** Timeline for the investigational group

Type	Screening^a^	Baseline^a^	Treatment				End of treatment (EOT)^h^	Follow-up				End of study (EOS)
Visit name	Screening	D0	W2	W4	W6	W8	W12 ~ (Every 4 W)	EOT + 3 M	EOT + 6 M	EOT + 9 M	EOT + 12M^i^	M18^i^
Weeks (w)	− 14 ~ 0 days	0	2 W	4 W	6 W	8 W	12 W/16 W/20 W/24 W /28 W/32 W	EOT + 13 W	EOT + 26 W	EOT + 39 W	EOT + 52 W	78 W
Visit window	n-a	n-a	± 4 days	± 4 days	± 4 days	± 4 days	± 2 weeks	± 6 weeks	± 6 weeks	± 6 weeks	± 6 weeks	± 6 weeks
Consent	O											
Randomization		O										
Medical history	O											
Physical exam	O	O	O	O	O	O	O	O	O	O	O	O
Xpert MTB/RIF assay	O^e^											
Sputum AFB smear	O^e^	O^e^	O	O	O	O	O	O	O	O	O	O
TB culture (liquid)	O^e^	O^e^	O	O	O	O	O	O	O	O	O	O
DST^b^	With first/reverted cultured MTB											
Chest X-ray	O^e^	O^e^		O		O	O	O	O	O	O	O
Chemistry^c^	O^e^	O^e^	O	O	O	O	O^h^					
Complete blood count	O^e^	O^e^	O	O	O	O	O^h^					
HIV	O^e^											
Urine (or blood) HCG^d^	O	O	O	O	O	O	O^h^					
HBV/HCV^f^		O^e^										
Compliance of drug intake			O	O	O	O	O^h^					
Adverse drug reaction			O	O	O	O	O^h^	O				
Other medication^g^	O		O	O	O	O	O^h^					

^a^ It can be performed with the baseline visit if all screening results can be checked on the day

^b^ Drug susceptibility test for isoniazid, rifampicin, ethambutol, pyrazinamide, streptomycin, kanamycin, amikacin, capreomycin, ofloxacin, levofloxacin, moxifloxacin, prothionamide, cycloserine, rifabutin, and para-aminosalicylic acid (Omitted for the patients whose results are already reported)

^c^ Test items according to the standard treatment guidelines (refer to 6. Study procedures)

^d^ Performed for women of childbearing age tested within 7 days

^e^ The existing test results can be extracted and collected without additional testing if the previous test was performed within 4 weeks (based on the report day for the TB culture)

^f^ Since HBsAg and Anti-HCVAb are not excluded even if they are positive, drugs can be administered even before the results are reported

^g^ Confirmation of concomitant drugs, especially immunosuppressants including oral steroids

^h^ The date of the end of treatment is determined according to the time of culture conversion to negative. A visit every 4 weeks until EOT and every 3 months after EOT. The test is not performed after EOT

^i^ If the 78-week visit (EOS) after randomization arrives earlier than the EOT + 12 M visit, the EOT + 12 M visit is omitted, and the EOS visit proceeds

### Definitions

Culture of *M. tuberculosis* will be considered to be converted to negative when two or more consecutive cultures, taken at different visits, are found to be negative in liquid medium. When a participant cannot produce sputum after the first negative culture sputum, they will be considered as having achieved culture conversion. The submission date of the first confirmed negative sputum culture will be regarded as the date of culture conversion. If *M. tuberculosis* is found to be re-cultured two or more times following a negative culture conversion, this will be termed culture reversion [18]. Treatment success is defined as achieving negative culture conversion and maintaining negative cultures till the end of treatment.

The sum of treatment failure, recurrence, death during treatment (except for accidents and suicide), loss to follow-up, and withdrawal from the study will be designated as “unfavorable outcomes.” Treatment failure will be defined as participants who fail to achieve culture conversion during treatment period, or as participants using second-line anti-TB drugs for more than 4 weeks. Recurrence will be assigned to participants that indicate the presence of *M. tuberculosis* in sputum cultures for two or more times after the end of treatment.

Adverse events will be defined when undesirable medical events have occurred in participants, irrespective of a causal relationship with the treatment [19]. When adverse events result in death, life-threatening conditions, patient hospitalization or prolongation of existing hospitalization, persistent or significant disability or incapacity, or a congenital anomaly or birth defect, the events will be classified as serious adverse events. The severity of each adverse event will be assessed based on Common Terminology Criteria for Adverse Events (CTCAE) version 5.0 [20].

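### The no-sputum exception to culture conversion has no bound and no rule for a later positive, so time to culture conversion, and with it the investigational end-of-treatment date, can be set too early

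*Protocol article*

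**What the plan says.** All places are in the Protocol article.

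- **Main rule (Definitions).** Conversion requires "two or more consecutive cultures, taken at different visits, are found to be negative in liquid medium".
- **Exception (Definitions).** "When a participant cannot produce sputum after the first negative culture sputum, they will be considered as having achieved culture conversion". No number of missed visits, no period and no condition on later sputum is attached.
- **Date (Definitions).** "The submission date of the first confirmed negative sputum culture will be regarded as the date of culture conversion". When the exception is used there is only one negative culture, so the date falls on that culture.
- **Reversion (Definitions).** The organism must be "re-cultured two or more times following a negative culture conversion, this will be termed culture reversion". A single later positive does not meet this.
- **End of treatment, investigational arm.** The Investigational group section states: "High-dose rifampicin and isoniazid will be administered until 12 weeks after the date of sputum culture negative conversion". Table 4, footnote h, agrees: "The date of the end of treatment is determined according to the time of culture conversion to negative".
- **End of treatment, control arm.** Table 3, footnote h, sets it by standard-of-care guidelines, not by the conversion date.
- **Missed sputum (Treatment visits).** Participants who produce none are to be encouraged to do so, and failure to produce is not a violation. Visits are every 2 weeks to week 8, then every 4 weeks to the end of treatment.
- **Use of conversion (Study outcomes, Definitions).** Time to culture conversion is a secondary outcome. Conversion also enters the definitions of treatment success and treatment failure.

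**The concern.** The main rule asks for a second negative because one negative culture can be a chance result in a participant who is still positive. The exception removes that safeguard exactly when the confirming specimen is absent, and nothing in the text restores it when sputum is obtained again and grows *M. tuberculosis*. Had a sputum been produced at the missed visit and been positive, the first negative could not have qualified. Missing data can therefore give an earlier conversion date than observed data would.

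Two things are at stake. One is the validity of time to culture conversion, which the plan compares between arms by Kaplan–Meier and log-rank. The other is the length of investigational treatment, which hangs on the same date. The definition is identical in both arms, but only in the investigational arm does the date end treatment.

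**Working it through.** The plan gives no figure for missing sputum or false-negative cultures, so there is none to reproduce on this point. Its sample size is not in dispute: 2 × 0.10 × 0.90 × (1.960 + 0.842)² / 0.06² = 392.4, so 393 per group, and 393 / 0.85 gives 463. Nothing below changes it.

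**Step 1. Score example sequences on the visit schedule** (N = negative, P = positive, M = no sputum; W2 is positive in each). The literal reading applies the exception at the first missed specimen. The bounded reading applies it only if no positive comes before a confirming negative. The end-of-treatment columns add 12 weeks to the conversion date, as the Investigational group section does.

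| Sequence from W4 | Literal: conversion / end of treatment | Bounded: conversion / end of treatment | Gap |
|---|---|---|---|
| W4 N, W6 M, W8 P, W12 N, W16 N | W4 / W16 | W12 / W24 | 8 weeks |
| W4 N, W6 M, W8 P, W12 P, W16 N, W20 N | W4 / W16 | W16 / W28 | 12 weeks |
| W4 N, W6 M, W8 N, later all N | W4 / W16 | W4 / W16 | 0 |
| W4 N, no sputum again | W4 / W16 | W4 / W16 | 0 |

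In the first row the single W8 positive does not meet the reversion definition, so nothing stated undoes W4. In the second row W8 and W12 do meet it, but the Definitions section does not say what reversion does to the conversion date. The readings differ only when a positive follows the gap.

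**Step 2. Size, on stated assumptions.** Let s be the probability that a still-positive participant gives a negative culture, and m the probability of no sputum at the next visit. Assume that cultures are independent, that missing sputum is unrelated to culture status, and that a later sputum is obtained. Neither s nor m is in the documents.

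- Confirmation by a second negative: s × s.
- Literal exception: s × [m + (1 − m)s].
- Ratio: [m + (1 − m)s] / s.

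| s | Two negatives | Literal, m = 5% | Literal, m = 30% | Ratio |
|---|---|---|---|---|
| 0.10 | 0.010 | 0.0145 | 0.037 | 1.45 to 3.7 |
| 0.20 | 0.040 | 0.048 | 0.088 | 1.2 to 2.2 |
| 0.30 | 0.090 | 0.1005 | 0.153 | 1.1 to 1.7 |

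For example, at s = 0.10 and m = 0.30: (0.30 + 0.70 × 0.10) / 0.10 = 3.7.

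**Step 3. Other outcomes in the first sequence.**

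- *Treatment success* needs conversion and negatives maintained to the end of treatment. Dated at W4, the W8 positive breaks maintenance and the participant does not succeed. Dated at W12, the same participant can succeed.
- *Treatment failure* through non-conversion does not arise under either date, because W12 and W16 are two consecutive negatives.
- *Recurrence* (two or more positive cultures after the end of treatment) is an unfavorable outcome, so disease returning after an early stop would be counted.

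**The case against.** The strongest reply is that the exception may be meant for lasting inability to produce sputum. The Treatment visits section asks that such participants be encouraged to expectorate, which suggests more than one skipped specimen. On that reading the W4/W6/W8 example never triggers the exception. This is possible, but the text does not say so, and sites have to apply the text. Accepting absence of sputum is also not wrong in itself; the last two sequences in the first table show no harm.

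Further points stand and limit the concern:

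- A single positive leaving conversion in place is not peculiar to the exception. Under the strict rule, two negatives followed by one positive also stay converted. What the exception adds is that no second negative was ever obtained.
- A reader might compare s with s² and infer 3 to 10 times as many false conversions (0.30 against 0.09, 0.10 against 0.01). That holds only if every such participant misses the next specimen, which nothing in the documents supports.
- A reader might infer that early conversion flatters every endpoint. For treatment success the example goes the other way, and for the primary outcome it changes nothing.
- The trial is open-label ("Both participants and treating physicians will be aware of allocation information"), and a reader might infer that sites would record missing sputum selectively in the investigational arm. The documents give no evidence of this. They show only that the date has a treatment consequence in one arm.
- Moving the conversion date in the protocol definition itself would move investigational end of treatment by 8 to 12 weeks in these sequences. A statistical remedy must therefore stay within the analysis definition.

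**Conclusion.** The concern holds as a defect in a stated definition: the exception is unbounded and silent on a positive result after the gap. Followed literally, it dates conversion 8 weeks too early in the main example, against the protocol's own two-negative standard. The same date gives W16 instead of W24 for investigational end of treatment.

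The outcome directly affected is time to culture conversion. How often this happens cannot be derived from the documents. The 1.1- to 3.7-fold increase applies to still-positive participants only and rests on the assumed ranges for s and m, on independence, and on missing sputum being unrelated to culture status. It is not a trial-wide rate.

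The documents do not support reading this as a demonstrated bias in the primary non-inferiority comparison. A participant deemed converted can no longer be a treatment failure through non-conversion, so some effect is possible. But the example shows none, and the recurrence definition catches part of any harm from stopping early. The net direction is uncertain.

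**What to change.** 1. For the analysis of time to culture conversion, let the single-negative exception count only if no positive culture is obtained before a confirming negative. Otherwise date conversion at the first of the next qualifying negatives. A participant who never produces sputum again keeps the exception.
2. Add a sensitivity analysis of time to culture conversion under the strict two-negative rule, with no exception.
3. Report by arm how many conversions rest on the exception, and how many of those were followed by a positive culture.
4. Reconcile the exception and the reversion rule in Definitions with the end-of-treatment rule in the Investigational group section and Table 4, footnote h. No clinical rule is proposed here.

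The cost is definition wording, one extra analysis and a count. No new samples are needed and the sample size is unchanged. The downside is slightly later conversion dates for a few participants in that analysis. Until item 4 is settled, the analysis date may differ from the date used to end treatment.

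### A participant with no earlier negative culture who yields no sputum on treatment can never meet the conversion rule, so is a primary-endpoint failure with no investigational end-of-treatment date

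*Protocol article*

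**What the plan says.** All references are to the protocol article.

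- **Conversion (Definitions).** The rule is met when "two or more consecutive cultures, taken at different visits, are found to be negative in liquid medium". Missing sputum has its own clause: "When a participant cannot produce sputum after the first negative culture sputum, they will be considered as having achieved culture conversion". The date is then fixed: "The submission date of the first confirmed negative sputum culture will be regarded as the date of culture conversion".
- **Failure (Definitions).** "Treatment failure will be defined as participants who fail to achieve culture conversion during treatment period"; prolonged second-line drug use is the alternative route. Failure is one component of the unfavorable outcome, and so of the primary endpoint.
- **Investigational treatment (Investigational group).** Three drugs are given "until culture conversion (liquid medium) is confirmed". The stopping rule is: "High-dose rifampicin and isoniazid will be administered until 12 weeks after the date of sputum culture negative conversion". Table 4, footnote h, likewise ties the end of treatment in this arm to conversion. In the control arm, Table 3 ties it to standard-of-care guidelines.
- **Who can enter (Study population).** Adults qualify "whose sputum (or bronchoscopic specimen) is positive for Xpert MTB/RIF assay or" for *M. tuberculosis* on culture, so a positive sputum culture is not needed. Up to 7 days of prior TB medication is allowed.
- **Missing sputum (Treatment visits).** "Participants who cannot produce sputum will be encouraged to expectorate sputum". If they still cannot, this is not a protocol violation.
- **Analysis sets (Statistical analysis).** The primary mITT set requires only one dose of study drug. The per-protocol set requires 10 of 12 planned weeks in the investigational arm.

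**The concern.** One definition does several jobs. It sets how long investigational patients are treated, decides treatment failure in both arms, and defines treatment success and time to conversion.

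The main problem is the missing-sputum clause. It helps only a participant who already has a negative culture. Someone whose baseline sputum culture was positive, or who had none because entry was by bronchoscopic specimen, and who then brings up no sputum, cannot satisfy either route to conversion. A patient whose cough has resolved is then counted in the same way as one with persistently positive cultures. In the investigational arm the printed rules also give no date on which to stop treatment. In an open-label trial, sites would have to improvise both the duration and the classification.

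The lesser problem is that the dating rule does not say that the negative sample must be taken on treatment. Part of the 12 weeks could then be credited before study drug has acted, and time to conversion could be zero.

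**Working it through.** **Inputs.** Conversion, dating and failure rules: Definitions. Treatment length, conversion date plus 12 weeks: Investigational group. Liquid cultures at screening, D0, W2, W4, W6, W8 and then every 4 weeks: Table 4. 10% unfavorable in both arms, 6% margin, one-sided 2.5%, 80% power, 15% dropout: Sample size calculation.

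**Plan's own figure.** n per arm = (1.960 + 0.842)² × 2 × 0.10 × 0.90 / 0.06² = 7.849 × 0.18 / 0.0036 = 392.4, so 393. With dropout, 393 / 0.85 = 462.4, so 463 per arm and 926 in total. All three figures reproduce.

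**Main point: no earlier negative and no on-treatment sputum.**

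1. Two consecutive negatives: not possible, because no sample is available.
2. One negative followed by no sputum: not met, because there is no first negative.
3. So there is no conversion and no conversion date.
4. No conversion during treatment is treatment failure, in either arm.
5. The participant was dosed, so remains in the mITT set and in the primary analysis.
6. Investigational end of treatment = conversion date + 12 weeks = undefined. The 10-of-12-week criterion has no starting date. Control treatment length is unaffected.

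Effect of one such participant, not otherwise unfavorable, on the arm's rate:

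- all randomized: 1/463 = 0.216 percentage points
- planned evaluable number: 1/393 = 0.254 percentage points

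**Lesser point: negatives before treatment.** End-of-treatment week = week of first confirmed negative + 12.

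| First negative | Condition | End of treatment | Days from D0 |
|---|---|---|---|
| D0 | W2 also negative, or no sputum afterwards | 0 + 12 = W12 | 84 |
| W2 | only on-treatment samples count; W2 confirmed | 2 + 12 = W14 | 98 |

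Difference: 98 − 84 = 14 days, and 14/98 = 14.3%. If W2 is positive, D0 is not the conversion date and nothing is shortened.

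**The case against.** **On-treatment conversion is plainly meant.** The three drugs run until conversion, the Discussion describes 12 weeks following it, failure is judged during the treatment period, and Table 4 places screening and D0 outside its treatment columns. This stands, and it reduces the D0 issue to a wording point. It does not help the participant with no sputum, because that outcome is the same on either reading.

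**The article condenses a fuller protocol.** A footnote to the timeline tables points to a study-procedures section that is not shown, and a fallback stop date could be there. That is a fair caution about the missing date. But the article prints the conversion rule complete with its missing-sputum exception, and prints the failure rule that depends on it. The classification comes from stated text, not from a gap.

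**Counting absent evidence as unfavorable is defensible.** This stands in part. In an open-label non-inferiority trial, sputum provision could differ by arm, and a blanket exemption would let missing evidence count as success. That argues for a conditional rule with a sensitivity analysis.

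**Few participants may be affected.** This is possible. The case needs no earlier negative sputum culture and no sputum at any treatment visit, although participants are encouraged to produce it. The document gives no number either way.

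**Conclusion.** The point holds, mainly for participants without sputum. Under the rules as printed, an eligible participant with no earlier negative sputum culture and no on-treatment sputum is a primary-endpoint failure in either arm. In the investigational arm that participant also has no end-of-treatment date and no per-protocol clock. The size is 0.22 to 0.25 percentage points on an arm's rate per participant, against a 6-point margin, assuming the participant is not unfavorable for another reason.

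The dating issue is minor: at most 14 days (W12 against W14) for a D0 negative, assuming that W2 would be the first on-treatment negative.

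Three stronger readings are not supported:

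- A reader might infer that any D0 negative ends treatment at W12. It does so only if W2 is also negative or no sputum follows.
- A reader might count a screening negative at day −14 and reach W10 (−2 + 12; 70 days). The literal text allows it, but the evident on-treatment intent makes it an unlikely way for a site to apply the rule.
- A reader might infer lost power or a bias toward one arm. The number affected is not in the document, so any power figure would rest on an invented share. The failure rule is the same in both arms, and a difference in sputum provision is a risk, not something shown.

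**What to change.** - **Definitions:** state that the conversion date cannot precede the first sputum submitted after study drug starts.
- **Investigational group:** set a fixed fallback end of treatment for participants with no on-treatment sputum, no earlier than 12 weeks after the first dose. W14 is one reasonable choice, because it matches the earliest scheduled on-treatment conversion (W2 + 12). Count per-protocol completion against that period.
- **Definitions, both arms:** do not class a participant as a failure solely because no sputum could be produced when there is no positive on-treatment culture.
- **Statistical analysis:** add a sensitivity analysis that counts these participants as unfavorable.

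These changes belong together. With the dating rule alone, a participant with a D0 negative and no later sputum would no longer convert and would join the group without an end date.

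The cost is a protocol amendment in a trial that has been recruiting since November 2020, touching treatment length and a primary-endpoint component, and slightly longer treatment for a subgroup. The sample size calculation does not change. If the full protocol already contains a fallback stop date, that part of the fix reduces to a cross-reference.
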